#### Randomization and stratification

The first 20 patients will be enrolled to arm A or B based on a pretrial 1:1 random allocation list generated by the trial statistician and made available to the research team in sealed envelopes. After the first 20 patients, the statistician will provide the randomization result for each patient according to the adaptive design. If a patient discontinues participating in the study, his/her randomization code will not be reused, and the patient will not be allowed to re-enter the study.

#### Quantitative analysis

The following patient populations will be considered for analysis:Intention-to-treat (ITT) population: the ITT population is defined as all patients who are randomized. Patients in this population will be analyzed according to the treatment they were randomized to receive, regardless of any errors of dosing.Safety population: the safety population will be assessed per treatment arm. For arm A it includes all patients who have completed at least one administration of lapatinib, irrespective of starting treatment with capecitabine (safety population in arm A). For arm B it includes all patients allocated to arm B and who completed at least one administration of capecitabine (safety population in arm B).Per protocol (PP) population: the PP population includes all patients who started the allocated treatment and have been submitted to surgical treatment.Exploratory subgroup analysis (ESA) population: the ESA population includes patients with complete data for the exploratory biomarkers who did not have any major protocol violation.

All available efficacy and safety data will be included in data listings and tabulations. However, for primary endpoint analysis any missing information regarding the endpoint (loss to follow-up or death prior to surgery and refusal to undergo surgery) will be assumed as absence of pathologic complete response. The impact of this imputation will be tested with a sensitivity analysis. For assessment of the stopping rule of toxicity, loss to follow-up (after all efforts made to assess the reason for it have failed) will be considered to be due to a serious adverse event.

Demographic and baseline characteristics including gender, age, weight, height, clinical stage (American Joint Committee on Cancer’s 7th edition cTN status [40]), EGFR and HER-2 amplification status, and other parameters, as appropriate, will be summarized by treatment groups using descriptive statistics.

The proportion of pCR of each arm will be described and the efficacy of one arm over the other estimated by the posterior probability of superiority and its 95 % credible interval. The trial will be stopped for efficacy if the posterior probability of one arm being superior to the other is greater than 0.95 and for futility if the same probability is less than 0.05. Additionally, the trial stops for futility if the probability of arm A having an effect greater than 0.2 is less than 0.05. The posterior probability of superiority of arm A over arm B will be continuously calculated after the 30th patient outcome is known.

Adverse events will be described as absolute number of patients presenting any given adverse event during treatment, its proportion, and respective 95 % credible intervals. Data will also be summarized as total number of patients presenting at least one serious adverse event and its proportion. For analysis of serious adverse events, a summary posterior probability of a serious adverse event and its 95 % credible interval will be calculated. Patient accrual for arm A will be stopped for toxicity if there is evidence of a serious adverse event posterior probability (SAEPP) greater than 25 %. A conservative threshold of 0.5 will be used for the posterior probability of toxicity, meaning that the trial stops with moderate evidence (50 %) of SAEPP >25 % for arm A. A non-informative prior (Beta (1, 1)) for the proportion of toxic events was chosen. The boundary at each step is plotted in Fig. 3. Should this toxicity boundary be identified for arm A, accrual to the trial is interrupted for excess toxicity at a lapatinib dose level of 1250 mg/d. The trial will then restart with lapatinib at a dose level of 1000 mg/d in arm A, and the data from patients previously randomized to arm B will be used to adjust the prior distribution of pB necessary for random treatment allocation in the Bayesian framework previously defined. In this latter setting, should the toxicity boundary be crossed, accrual to the trial is stopped for toxicity and the combination of lapatinib with capecitabine as radiosensitizer will be considered too toxic for further study.

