#### Determination of sample size

The trial’s objective is to show the superiority of the lapatinib and capecitabine combination (arm A) over the standard capecitabine (arm B). Thus, the null hypothesis is defined as H_0_: pB ≥ pA, where pA and pB are the probabilities of a pCR for arms A and B, respectively.

The expected sample size calculations were conducted in the context of a Bayesian adaptive randomization design, with stopping rules for early evidence of efficacy/futility and evidence of toxicity. These calculations are based on simulated trial results, which require presetting maximum and minimum total sample size, minimum number of patients fairly randomized to each arm, minimum probability of randomization for each arm, prior distributions for the treatment effect, and stopping rules for efficacy/futility.

We chose a maximum of 80 patients, based on the feasibility of patient’s accrual during the proposed study period. A minimum of 30 patients should be enrolled in the study before stopping the trial due to early evidence of efficacy/inefficacy. However, accrual may stop before the enrollment of 30 patients if there is evidence of toxicity, as defined below. The first 20 patients enrolled in the study will be fairly (non-adaptively) randomized to both arms. During the adaptive randomization phase, the minimum probability of randomization for each arm is set at 0.1.

For arm A, a non-informative prior for treatment effect, i.e., pA ~ Uniform (0,1), and for arm B, a moderate informative prior for treatment effect pB ~ Beta (1.2, 8.8) are used, as shown in Figs. 1 and 2, respectively.

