The primary objective of the trial is to show that lapatinib-capecitabine radiochemotherapy is superior to capecitabine radiochemotherapy. The choice of complete pathologic response as the primary outcome measure allows such interpretation since it is a feasible and reproducible short-term endpoint and is reported to be associated with improved cancer-specific survival [7]. The choice to use full doses for each treatment component maximizes the probability of treatment response. As with any novel treatment combination, tolerability will be an important issue. The experimental arm has never been studied in this setting. Therefore, we have integrated into the Bayesian design a specific stopping rule to address this. This rule was designed to reproduce the performance of classic phase I trials, which are designed to explore the maximum tolerated dose of a given agent or combination while protecting as many patients as possible from excessive risks. The main anticipated toxicity is diarrhea; therefore, mandatory pre-emptive antidiarrheal medication will be recommended for every patient. Should excess toxicity be an issue with a standard dose of lapatinib, we have stipulated a reset of the trial with a lower dose of lapatinib. However, this should not impact the assessment of clinical value of this combination, as the lower dose level of lapatinib is still associated with a C_min_ above that which is required for antitumor effect. Additionally, the incorporation of a lead-in period of lapatinib together with tumor sampling before and after the 2-week lead-in period will provide further information on the pharmacodynamics of lapatinib and direct evidence of on-target effect.

This trial includes an exploratory biomarker program. This was designed to better understand the role that EGFR inhibitors and lapatinib in particular play in this setting and to identify potentially predictive biomarkers for response.

In conclusion, the LaRRC trial will inform on the role of dual inhibition of EGFR and HER-2 in the neoadjuvant treatment of resectable rectal cancer. The choice of a Bayesian adaptive randomization together with an initial lead-in treatment phase with lapatinib in the experimental arm provides the best chance to maximize the information collected while effectively balancing the risks and potential benefits for eligible patients.

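### As worded, the arm A toxicity rule is met by its prior alone and by one SAE in the first five patients, so it does not have the classic phase I performance the protocol claims for it

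*Protocol article*

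**What the plan says.** The rule is in the Protocol article, Quantitative analysis. The limit on the arm A SAE rate is 25%. The cut-off is set by "A conservative threshold of 0.5 will be used for the posterior probability of toxicity", explained as meaning that "the trial stops with moderate evidence (50 %) of SAEPP >25 % for arm A". The prior is given by "A non-informative prior (Beta (1, 1)) for the proportion of toxic events was chosen". On timing the text says only that "The boundary at each step is plotted in Fig. 3".

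Determination of sample size exempts toxicity from the 30-patient minimum: "accrual may stop before the enrollment of 30 patients if there is evidence of toxicity". No minimum number of arm A patients is given in the text.

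A first crossing interrupts accrual and restarts the trial at a lower lapatinib level. A second crossing ends it, and the combination is then regarded as too toxic to pursue. For this rule, a loss to follow-up that stays unexplained after all efforts "will be considered to be due to a serious adverse event".

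The Discussion states the intended behaviour: "This rule was designed to reproduce the performance of classic phase I trials". No crossing probabilities are printed for the toxicity rule, and the three sample-size scenarios name no SAE rate.

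**The concern.** A Beta(1,1) prior on an SAE rate is flat, but it is not neutral about a 25% limit: three quarters of its mass lies above that limit. With a cut-off of 0.5, the trial starts on the stopping side of its own rule, and early patients have to argue it back. A stop can then reflect the prior more than the data, and that is not the moderate evidence the section describes.

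The consequences are large. One crossing resets the trial and two end development of the combination. If crossings are common at SAE rates below the protocol's own limit, the efficacy comparison may be cut short or never reached. The stated equivalence to phase I performance would also mislead anyone relying on it.

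**Working it through.** **Inputs.** Limit 0.25, cut-off 0.5, prior Beta(1,1) and a boundary at each step come from Quantitative analysis. The 34 arm A patients are the scenario I expectation in Determination of sample size. Assumed here: true SAE rates of 5% to 40%, a look after every arm A patient with SAE status known at once, and a 3+3 cohort as the classic phase I design, with an SAE treated as its dose-limiting event. The visible text prints no toxicity figure, so there is none to reproduce.

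**Step 1: the posterior.** With x SAEs in n patients, P(rate > 0.25) = P(Beta(1+x, 1+n−x) > 0.25) = P(Bin(n+1, 0.25) ≤ x).

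- No data: 0.75.
- 0 of 1: 0.75² = 0.5625. Still above 0.5.
- 0 of 2: 0.75³ = 0.422. Below 0.5 for the first time.
- 1 of 1, 2, 3, 4, 5: 0.938, 0.844, 0.738, 0.633, 0.534. All cross. For 1 of 5: 0.75⁶ + 6 × 0.25 × 0.75⁵ = 0.178 + 0.356 = 0.534.
- 1 of 6: 0.445. Does not cross.

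If at least one SAE is required, the boundary is 1 SAE up to patient 5, 2 for patients 6–9, 3 for 10–13, 4 for 14–17 and 5 for 18–21.

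**Step 2: crossing probabilities.** These come from an exact patient-by-patient recursion to 34 arm A patients. At least one SAE is required to stop, which favours the protocol because it ignores the zero-SAE crossings. The 3+3 figure is 1 − [(1−p)³ + 3p(1−p)⁵]; at p = 0.10 it is 1 − [0.729 + 0.177] = 0.094.

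| True SAE rate | Rule, by patient 34 | Rule, first 6 patients | 3+3 cohort | Looks from patient 6, by 34 | Looks from patient 10, by 34 |
|---|---|---|---|---|---|
| 5% | 24% | 23% | 3% | 8% | 3% |
| 10% | 46% | 41% | 9% | 26% | 16% |
| 15% | 65% | 56% | 19% | 49% | 39% |
| 20% | 81% | 67% | 29% | 71% | 63% |

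At a 10% rate, 41 of the 46 percentage points arise by patient 5, since 1 − 0.9⁵ = 0.41. One SAE in three patients stops this rule, whereas a 3+3 cohort would expand. Reading the rule as a posterior mean above 25% gives the same stopping probabilities.

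**Step 3: two crossings.** If the restarted level has the same rate, 34 patients and a fresh prior, the probability is the square of the single-level figure: 0.240² = 6%, 0.460² = 21%, 0.653² = 43% and 0.807² = 65% at 5%, 10%, 15% and 20%.

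**The case against.** The strongest objection is that the operative boundary is in Fig. 3, which is not reproduced in the text available here. If its first look is at patient 6, the boundary there is 2 of 6. That single look crosses with probability 11%, 22% and 35% at 10%, 15% and 20%, close to the 3+3 figures of 9%, 19% and 29%. This stands as a limit on the one-in-five trigger, which follows from the text but may not be what the figure shows. It does not rescue the claim, because the looks continue: by patient 34 crossing reaches 26%, 49% and 71%.

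Second, the caution is disclosed and reasoned. The threshold is labelled conservative, the combination is new in this setting, a first crossing leads to a restart, and no document defines an acceptable SAE rate. How much false stopping to accept is partly the sponsor's judgement. That stands. The fault lies in the zero-event crossing and in the performance claim, not in caution itself.

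Third, three stronger readings are tempting and are not supported:

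- A reader might infer that the trial would stop before it began. With no patient observed there is nothing to stop; the point is where the prior sits, and the crossing probabilities do not rely on it.
- A reader might infer that a final too-toxic conclusion is likely at rates well below 25%. It is about 6% at a 5% rate, 21% at 10% and 43% at 15%, and of the rates examined below 25% it exceeds one half only at 20%, under the assumptions in step 3.
- A reader might infer that the rule counts SAEs through the visit after surgery. Table 1 collects adverse events at that visit, but Quantitative analysis describes adverse events during treatment and gives the stopping rule no window.

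**Conclusion.** The point holds as a conflict between the rule as worded and the performance claimed for it. The posterior results in step 1 are exact and depend only on the stated prior, limit and cut-off: the rule is met with no data, after 0 of 1, and by one SAE at any n from 1 to 5. The crossing probabilities of 24% to 81% at true rates of 5% to 20% rest on looks after each patient, 34 arm A patients and assumed SAE rates. The comparison with phase I rests on taking 3+3 as the classic design. A later first look weakens the result without removing it: starting at patient 10, crossing is near the 3+3 figure at a 5% rate, but 16% against 9% at 10% and 63% against 29% at 20%. Correction is needed because the rule can reset or end the trial.

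**What to change.** Reconcile the rule in Quantitative analysis, Fig. 3 and the Discussion:

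1. Word the rule so that neither the prior alone nor zero SAEs can meet it.
2. State the first look in the text, and make Fig. 3 agree.
3. Print the crossing probabilities over true SAE rates both below and above 25%.
4. Either withdraw the phase I performance claim, or have the sponsor recalibrate the prior or threshold to match it.
5. Report the concurrent arm B SAE rate beside any conclusion that the combination is too toxic.

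The 25% limit and the dose plan stay as they are.

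Items 1 to 3 and 5, and withdrawing the claim under item 4, take an amended paragraph, a checked figure and a sentence in the Discussion, with no extra patients or data. Recalibration is not free and is the sponsor's choice. As an illustration only, a 0.80 threshold from patient 3, with at most 40 arm A patients, lowers crossing at a 10% rate from 46% to 10%. It also lowers stopping at a 30% rate from 97% to 79%, and raises expected arm A exposure from 5.2 to 15.5 patients at 30% and from 2.9 to 8.2 at 40%. Any new calibration should be presented with both sides of that trade.

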**Fig. 3 Fig3:**
[figure not shown]
Boundary for early stop due to toxicity

Biomarkers will be described as the proportion of patients with the given biomarker present in the respective arm and their 95 % credible intervals. Identification of predictive biomarkers will be performed through logistic regression analysis. The model will test the association between activation of EGFR pathway at baseline and pCR (between group analyses) and the discriminatory ability of its inhibition on pCR on arm A (within group analysis). The following biomarkers will be included in the model: EGFR amplification; HER-2/neu amplification; MAPK phosphorylation status; AKT phosphorylation status; EGFR phosphorylation status at baseline (between group analysis) and at baseline and on day 14 biopsy specimens for patients in arm A (within group analysis). Odds ratios will be presented with their 95 % credible intervals, and the c-statistics (area under the receiver operating characteristic curve) will be computed.

### Ethical considerations

The protocol has been written, and the study will be conducted according to the ICH Harmonized Tripartite Guideline on Good Clinical Practice. All patients will be informed about the aims of the study, trial procedures, possible hazards and adverse events, the mechanism of treatment allocation, and procedures to ensure patient data confidentiality before enrollment.

The trial was submitted for ethical review by Portugal’s National Ethics Committee for Clinical Research and was approved on 7 February 2014, deliberation number 2014-RP-02-11.

During the trial, if a protocol amendment is deemed necessary and may significantly affect the safety of patients, the scope of investigation, or the scientific quality of the study, a prior favorable opinion from Portugal’s National Ethics Committee for Clinical Research and approval from the Portuguese National Authority of Medicines and Health Products will be sought before implementation. If a protocol amendment affects only administrative aspects of the study, both the Portuguese National Ethics Committee for Clinical Research and Portuguese National Authority of Medicines will be notified of such administrative changes, but prior approval will not be procured.

Clinical trial insurance has been taken out according to Portuguese law by the sponsor.

## Discussion

To our knowledge, this is the first trial to assess the efficacy of dual inhibition of EGFR and HER-2 as a radiosensitizer in resectable rectal cancer. The trial is designed to include an enriched population of patients with KRAS and NRAS wild-type rectal cancer due to evidence of lack of benefit from anti-EGFR strategies in KRAS or NRAS mutated colorectal tumors. However, the role of KRAS or NRAS mutations in localized rectal cancer is uncertain. There is no information on whether this subgroup of rectal cancer patients have a different prognosis compared to patients with activating mutations nor if absence of mutation in KRAS or NRAS is predictive of response to standard radiochemotherapy. Thus, a randomized trial with an active comparator was needed to answer this question. The choice of a randomized adaptive Bayesian design allows an optimized sample size as well as a concurrent comparator. This design optimizes the trial’s sample size and protects eligible patients from randomization to a weakly performing arm, thus improving our ability to decide whether further study of lapatinib in this setting is warranted [50, 51].

The primary objective of the trial is to show that lapatinib-capecitabine radiochemotherapy is superior to capecitabine radiochemotherapy. The choice of complete pathologic response as the primary outcome measure allows such interpretation since it is a feasible and reproducible short-term endpoint and is reported to be associated with improved cancer-specific survival [7]. The choice to use full doses for each treatment component maximizes the probability of treatment response. As with any novel treatment combination, tolerability will be an important issue. The experimental arm has never been studied in this setting. Therefore, we have integrated into the Bayesian design a specific stopping rule to address this. This rule was designed to reproduce the performance of classic phase I trials, which are designed to explore the maximum tolerated dose of a given agent or combination while protecting as many patients as possible from excessive risks. The main anticipated toxicity is diarrhea; therefore, mandatory pre-emptive antidiarrheal medication will be recommended for every patient. Should excess toxicity be an issue with a standard dose of lapatinib, we have stipulated a reset of the trial with a lower dose of lapatinib. However, this should not impact the assessment of clinical value of this combination, as the lower dose level of lapatinib is still associated with a C_min_ above that which is required for antitumor effect. Additionally, the incorporation of a lead-in period of lapatinib together with tumor sampling before and after the 2-week lead-in period will provide further information on the pharmacodynamics of lapatinib and direct evidence of on-target effect.

This trial includes an exploratory biomarker program. This was designed to better understand the role that EGFR inhibitors and lapatinib in particular play in this setting and to identify potentially predictive biomarkers for response.

In conclusion, the LaRRC trial will inform on the role of dual inhibition of EGFR and HER-2 in the neoadjuvant treatment of resectable rectal cancer. The choice of a Bayesian adaptive randomization together with an initial lead-in treatment phase with lapatinib in the experimental arm provides the best chance to maximize the information collected while effectively balancing the risks and potential benefits for eligible patients.

## Trial status

The trial is currently recruiting.

## Abbreviations

3D-RT: 3D conformal external beam radiation
CRM: Circumferential radial margin
CTV45: Clinical tumor volume 45 Gy
CTV50.4: Clinical tumor volume 50.4 Gy
CTCAE: Common Terminology Criteria for Adverse Events
DPD: Dihydropyrimidine dehydrogenase
EGFR: Epidermal growth factor receptor
ESA: Exploratory subgroup analysis
GTV: Gross tumor volume
HRM: High resolution melting
IMRT: Intensity modulated radiotherapy
ITT: Intention to treat
pCR: Pathologic complete remission
PP: Per protocol
PTV45: Planned target volume 45 Gy
PTV50.4: Planned target volume 50.4 Gy
SAEPP: Serious adverse event posterior probability
ULN: Upper limit of normality
VMAT: Volume modulated arc therapy
